### Study overview

#### Objectives

The primary objective is to determine the effectiveness of a progressive and individualised walking and education program compared to a no-treatment control group, for reducing recurrences of LBP (primary outcome). The trial hypothesis is that the participants randomised to the intervention arm will experience a greater number of days from the time of randomisation to the first self-reported recurrence of an episode of LBP (i.e. superiority). The null hypothesis is that there is no difference in days to the first self-reported recurrence between the two arms of the trial.

Secondary objectives include determining whether the walking and education program:Improves health-related quality of life and disability.Is cost-effective from a societal perspective, including data on healthcare utilisation and productivity loss (work absenteeism) due to LBP.Increases levels of physical activity.Is acceptable and adhered to, based on a series of compliance measures.Results in any greater risk of adverse events when compared to no treatment.

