##### Adverse events outcomes

Adverse event data will be self-reported and collected at quarterly intervals (months 3, 6, 9 and 12). The following definitions will be used:

*Adverse event*, any untoward medical occurrence in a participant that does not necessarily have a causal relationship with this treatment.*Serious adverse event*, any adverse event that resulted in death, was life-threatening, required hospitalisation, or resulted in persistent or significant disability or incapacity. These events do not necessarily have a causal relationship with the treatment.

Adverse events and serious adverse events will be coded according to the International Classification of Diseases (ICD-11) using three-digit codes [17].

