#### Intervention

Participants allocated to the intervention group receive an individualised and progressive walking and education program, provided by registered physiotherapists trained for the trial, from 25 private practice sites across the states of New South Wales and Queensland in Australia. Initial plans assumed the intervention would involve six sessions comprising an even split of face-to-face and telehealth consultations for all participants. Due to COVID-19, and government advice in Australia related to the pandemic, temporary restrictions were placed on the provision of face-to-face consultations and so some patients received all elements of the intervention via telehealth. The broad aim of these sessions is to design a progressive and individually tailored walking program with each participant, targeting a dosage of walking of 5 times per week, for at least 30 min by 3 months into the intervention.

The delivery of the intervention has been framed around the principles of health coaching, with the intention of supporting behaviour change and optimising compliance. Another method to facilitate compliance is the provision of a pedometer and walking diary to act as motivators in completing the program and to provide participants with a degree of accountability. The education component of the intervention focuses on a modern understanding of LBP, aimed to reduce the threat and fear associated with pain, alongside advice related to strategies to reduce the risk of a recurrence of LBP. Participants in the control group receive no intervention as part of their involvement in the trial. Detailed information related to the intervention and control groups can be found in the published protocol [7].

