### Statistical analysis

#### Analysis principles

All analyses will be conducted using R software (version 4.2.2 or above) or STATA (version 17.0 or above). Analyses of the primary and secondary outcomes will be conducted by a statistician (member of the trial team), taking no part in participant recruitment or data collection. Analyses will follow intention-to-treat principles, with all participants analysed according to their randomised allocation. A masked sample of the data will first be used to trial and confirm statistical procedures. Next, the fully masked dataset will be used, with data interpretation occurring prior to unblinding of group allocation. There is no intention to conduct interim analyses.

Categorical variables will be summarised by frequencies and percentages. Continuous variables will be reported using standard measures of central tendency and dispersion, either mean and standard deviation (SD) or median and interquartile range, depending on the shape or skewness of the data. A *p*-value < 0.05 will be considered statistically significant. A 95% confidence interval (CI) will be reported to aid the interpretation of precision and the clinical importance of findings.

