##### Adverse event analyses

For the measures of adverse events, we will represent the frequency and proportion of participants who experienced an adverse event, and these will be compared between groups using Fisher’s exact test as we expect the incidence of adverse events to be low (see Table 3).

**Table 3 Tab3:** Adverse and serious adverse events

	**Intervention group (*****n***** = xxx)**	**Control group (*****n***** = xxx)**	***p*****-value**
Serious adverse events			
Total	nEVT/nPAT (%)	nEVT/nPAT (%)	*p* = 0.xxx
Adverse event A^a^	nEVT/nPAT (%)	nEVT/nPAT (%)	
Adverse event B^a^	nEVT/nPAT (%)	nEVT/nPAT (%)	
Adverse event C^a^	nEVT/nPAT (%)	nEVT/nPAT (%)	
Etc.^a^	nEVT/nPAT (%)	nEVT/nPAT (%)	
Adverse events			
Total	nEVT/nPAT (%)	nEVT/nPAT (%)	*p* = 0.xxx
Adverse event A^a^	nEVT/nPAT (%)	nEVT/nPAT (%)	
Adverse event B^a^	nEVT/nPAT (%)	nEVT/nPAT (%)	
Adverse event C^a^	nEVT/nPAT (%)	nEVT/nPAT (%)	
Etc.^a^	nEVT/nPAT (%)	nEVT/nPAT (%)	

^a^Example categories which will be revised based on observation of final free-text data responses

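### Adverse events are compared between arms only as two all-cause totals; one walking-related category, named by code in advance and reported with an interval, would be a cheap improvement

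*SAP article*

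**What the plan says.** All references are to the SAP article.

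- **Objectives.** One secondary objective is whether the programme "Results in any greater risk of adverse events when compared to no treatment". No particular kind of harm is named.
- **Adverse events outcomes.** An adverse event is "any untoward medical occurrence in a participant that does not necessarily have a causal relationship with this treatment". Events are self-reported every quarter to month 12. The same section fixes the coding: "Adverse events and serious adverse events will be coded according to the International Classification of Diseases (ICD-11) using three-digit codes".
- **Adverse event analyses.** The measure is the share of participants in each arm with at least one event. On the method and the reason for choosing it, the section says that "these will be compared between groups using Fisher’s exact test as we expect the incidence of adverse events to be low". No expected rate is given.
- **Table 3.** A p-value appears in two rows only, the total for serious adverse events and the total for adverse events. The category rows give counts and percentages by arm and nothing else. No row has an effect estimate or a confidence interval. The category rows are marked "Example categories which will be revised based on observation of final free-text data responses".
- **Analysis principles.** The general threshold is that a p-"value < 0.05 will be considered statistically significant", and 95% CIs are promised in general terms.
- **Intervention.** The walking programme is described as "targeting a dosage of walking of 5 times per week, for at least 30 min by 3 months into the intervention".

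**The concern.** The totals count every untoward occurrence over 12 months. The harms that a walking programme could plausibly add, such as lower-limb musculoskeletal injury or pain and falls, are a subset of those events. Events unrelated to walking add similar numbers to both arms. They leave the absolute difference nearly unchanged and increase its variance, so a real excess in the subset is harder to detect in the total.

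The rows where such an excess would show are the ones without a comparison. Their content is also open: the footnote lets them take shape once the responses have been read, and it does not say that they follow the ICD-11 codes. What is at stake is how informative the answer to the stated safety objective will be. A non-significant total would say little about walking-related harm, and any reading of a category row would rest on a grouping chosen after the event.

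**Working it through.** **No figure to reproduce.** The plan gives no rate, power or sample size for adverse events. Its one sample-size figure (349 per group) concerns the primary outcome and does not bear on this point. Every adverse-event rate below is an assumption.

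**Inputs**
- 701 randomised (Background), taken as 351 intervention and 350 control. The split is an assumption.
- Two-sided Fisher's exact test (Adverse event analyses) at 0.05 (Analysis principles).
- *s* = the risk of at least one walking-related event in an arm.
- *b* = the risk of at least one unrelated event, assumed equal in both arms and independent of *s*.

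**Formula.** Risk of any event in an arm: *t* = 1 − (1 − *b*)(1 − *s*). The difference between arms in the total is therefore (1 − *b*) × (difference in *s*), while the risks themselves move up to where the binomial variance is larger.

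**Worked case, 8% versus 3%**
- Category alone: difference 5 percentage points, exact power 80%.
- *b* = 5%: *t* = 1 − 0.95 × 0.92 = 12.6% versus 1 − 0.95 × 0.97 = 7.85%. Difference 4.75 points, power 50%.
- *b* = 20%: *t* = 1 − 0.80 × 0.92 = 26.4% versus 1 − 0.80 × 0.97 = 22.4%. Difference 4.0 points, power 21%.

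**Range.** Power by summing exact binomial probabilities over all outcomes that Fisher's test rejects:

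| Walking-related events, intervention vs control | Category alone | Total, *b* = 5% | 10% | 20% | 30% | 50% |
|---|---|---|---|---|---|---|
| 16% vs 8% | 89% | 76% | 63% | 44% | 31% | 18% |
| 10% vs 4% | 86% | 62% | 46% | 29% | 20% | 12% |
| 8% vs 3% | 80% | 50% | 35% | 21% | 15% | 10% |
| 6% vs 2% | 74% | 38% | 26% | 15% | 11% | 8% |
| 4% vs 2% | 28% | 13% | 9% | 7% | 6% | 6% |

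The loss is present even at *b* = 5%, the setting closest to the low incidence that the plan expects. In the last row the category itself is too rare for a test to be useful, and an interval would mainly show how little is known.

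**Testing every category is not the answer.** With independent tests at 0.05, the chance of at least one false signal is 1 − 0.95^5 = 23% for five categories and 1 − 0.95^10 = 40% for ten.

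**The case against.** The case for leaving the plan as it is has several parts, and much of it stands.

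- **The test matches the objective.** The objective asks about adverse events in general, and the tested proportion answers that. This stands: a walking-related category is an addition, not a correction of a mismatch.
- **Nothing is hidden.** Category counts are printed by arm. At 16% versus 8% the table would show about 56 versus 28 participants. This also stands. A reader might infer that a doubling could go unseen, and Table 3 does not support that. What is missing is an estimate with an interval on a category fixed in advance.
- **Descriptive categories limit false signals.** This is correct, as the 23% and 40% above show. It argues against testing all categories, not against naming one.
- **Serious events are tested separately.** They are, so it would be wrong to say that there is a single comparison. That second total is also all-cause.
- **Incidence is expected to be low.** Low background reduces the dilution but does not remove it (80% to 50% at 8% versus 3%). If the category is also rare, the gain in power is small.

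Two stronger readings are tempting and are not supported. A reader might take the footnote and the ICD-11 statement as contradictory. They are not: free text has to be read before it can be coded, the table rows are placeholders, and both statements can be followed together. What can be said is that the footnote does not refer to the coding. A reader might also infer that shaping categories from the free text would unmask the arms. The document does not say that responses mention the programme, nor who codes them, and it keeps outcome collectors and analysts blinded.

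**Conclusion.** The point holds as a cheap improvement. Both between-arm adverse-event comparisons are all-cause totals, no walking-related category is named in advance, and the category rows are not tied to the coding that the plan itself specifies. A walking-specific excess would be visible but diluted where it is tested, and would have no interval where it is visible.

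The direction of the dilution follows from the definition of the total. Its size does not come from the document. It depends on the assumed rates, on unrelated events being equal and independent between arms, and on a near-equal split of the 701 participants. Under those assumptions, 8% versus 3% goes from about 80% power on the category to between about 50% and 10% on the total. For a rare category, such as 4% versus 2%, power is low either way. The primary result is not affected.

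**What to change.** 1. Replace the Table 3 footnote with a statement that the rows are defined by the ICD-11 codes given under Adverse events outcomes.
2. Before the masked review, name by code list one walking-related category, for example lower-limb musculoskeletal injury or pain, and falls.
3. For that category, report the number of participants with at least one event per arm and the risk difference with 95% CI, beside the two totals. Leave the remaining categories descriptive.
4. Label the added comparison as not adjusted for multiplicity.

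The cost is SAP wording and one table row, from data already collected and already due to be coded. The downside is one more safety comparison, whose interval may be wide if events are rare.

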##### Handling of missing data

A completeness index will be used to calculate the completeness of primary survival data [24]. Participants who are lost to follow-up will be censored on the day they last provided data, and those with no available outcome data will be censored at day one. All other available primary data will be used until recurrence (i.e. primary outcome) or reaching the end of the data collection period (i.e. minimum 12 months).

For the remaining secondary effectiveness outcomes, the number of missing observations will be reported at each relevant timepoint (i.e. months 3, 6, 9 and 12). In cases where more than 10% of the outcome data is missing, multiple imputations will be used to conduct sensitivity analyses. The need to impute will be confirmed at the time of the masked review of the data.

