#### Sample size and randomisation

A sample size calculation indicated that 349 participants per group (698 total) would provide 80% power to detect a 25% relative reduction in recurrence rates of *activity-limiting LBP* (i.e. primary outcome) in the intervention group, compared to the control group. We used a conservative estimate of 30% recurrence rate at 12 months in the control group, a rate observed in previous work by Stanton et al. [19] A 25% relative reduction (from 30 to 22.5%) is large enough to have important public health implications for such a simple intervention. Specifications include a two-sided log-rank test, Type-I error = 0.05, 24-month accrual period, and 12-month follow-up period. Sample size calculations allowed for 1% loss to follow-up per month.

Randomisation to intervention or control was conducted using a pre-generated schedule and allocation concealment was ensured at the patient level. Randomisation used randomly permuted blocks of 4, 6 and 8 and participants were stratified by history of > 2 previous lifetime episodes of LBP (known to be a prognostic factor for recurrence) [3], and recruitment from the community versus clinician referral.

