#### Secondary analyses

##### Effectiveness outcome analyses

For the outcomes of *any LBP recurrence* or a *care-seeking recurrence of LBP*, an analogous survival analysis to that of the primary outcome detailed above will be conducted.

To test the effects of the intervention on continuous secondary outcomes, between-group comparisons will be conducted using multiple linear mixed-effects regression combining all available post-randomisation measurements (at either months 3, 6, 9 or 12 depending on outcome collection). Transformations will be applied to meet model assumptions, if needed. Linear mixed modelling will be used to take account of the correlation between measurements within an individual for repeated measurements over time. A template has been provided for how the data will be reported (see Table 2).

**Table 2 Tab2:** Secondary outcomes

	**Intervention (*****n***** = xxx)**	**Control (*****n***** = xxx)**	**Mean difference (95% CI), *****p*****-value**
Disability—RMDQ			
Month 3	xx.x (SD), *n*	xx.x (SD), *n*	xx.x (xx.x to xx.x),* p* = 0.xxx
Month 6	xx.x (SD), *n*	xx.x (SD), *n*	xx.x (xx.x to xx.x),* p* = 0.xxx
Month 9	xx.x (SD), *n*	xx.x (SD), *n*	xx.x (xx.x to xx.x),* p* = 0.xxx
Month 12	xx.x (SD), *n*	xx.x (SD), *n*	xx.x (xx.x to xx.x),* p* = 0.xxx
Health-related QoL – EQ-5D-5L			
Month 3	xx.x (SD), *n*	xx.x (SD), *n*	xx.x (xx.x to xx.x),* p* = 0.xxx
Month 6	xx.x (SD), *n*	xx.x (SD), *n*	xx.x (xx.x to xx.x),* p* = 0.xxx
Month 9	xx.x (SD), *n*	xx.x (SD), *n*	xx.x (xx.x to xx.x),* p* = 0.xxx
Month 12	xx.x (SD), *n*	xx.x (SD), *n*	xx.x (xx.x to xx.x),* p* = 0.xxx
Self-reported Physical Activity—IPAQ			
Month 3	xx.x (SD), *n*	xx.x (SD), *n*	xx.x (xx.x to xx.x),* p* = 0.xxx
Month 12	xx.x (SD), *n*	xx.x (SD), *n*	xx.x (xx.x to xx.x),* p* = 0.xxx
ActiGraph measure at 3 months^a^			
Steps per day	xx.x (SD), *n*	xx.x (SD), *n*	xx.x (xx.x to xx.x),* p* = 0.xxx
Brisk Steps per day^b^	xx.x (SD), *n*	xx.x (SD), *n*	xx.x (xx.x to xx.x),* p* = 0.xxx
MVPA minutes per day	xx.x (SD), *n*	xx.x (SD), *n*	xx.x (xx.x to xx.x),* p* = 0.xxx

*EQ-5D-5L* EuroQol 5-Dimension 5-Level, *IPAQ* International Physical Activity Questionnaire, *MVPA* Moderate-vigorous physical activity, *RMDQ* Roland-Morris Disability Questionnaire

^a^Data in above table represents a minimum 4-day, and maximum of 7-day wear period. Only data for participants whose dataset met the minimum wear time requirement of 10 h/day are included

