##### Economic evaluation analyses

The economic evaluation will be conducted from the societal perspective as the primary analysis, whilst the Australian health system perspective will be used for sensitivity analyses. The time horizon of the economic analysis is 12 months.

For the economic evaluation, missing cost and effect data will be imputed using multivariate imputation by chained equations with predictive mean matching [21]. The imputation model will include variables differing between groups at baseline as well as those predicting the missingness of follow-up cost and effect data. Cost and effect differences will be estimated using seemingly unrelated regression analyses, in which two regression equations are modelled simultaneously and cost and effect differences are adjusted for their possible correlations through correlated error terms. Cost and effect differences will be adjusted using the same covariates as the primary effectiveness analyses, in addition to work status and baseline utility values for QALYs [22]. To handle the right skewed nature of cost data, uncertainty surrounding cost differences will be estimated using bias-corrected and accelerated bootstrapping (5000 replications) [23].

Incremental cost-effectiveness ratios (ICERs) will be calculated by dividing the between-group difference in costs by the between-group difference in effects (i.e. cost per recurrence prevented, and cost per QALY gained). The uncertainty surrounding ICERs will be estimated using bootstrapping as well (5000 replications) and graphically presented on cost-effectiveness planes. Cost-effectiveness acceptability curves will be estimated to show the probability of the intervention being cost-effective for a range of willingness to pay (i.e. maximum amount decision-makers are willing to pay per unit of effect gained). Sensitivity analyses will be performed to assess the robustness of the results based on a complete-case analysis and an analysis from the Australian health system perspective.

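### For RMDQ and EQ-5D-5L, the multiple-imputation sensitivity analysis ordinarily keeps the main model's missing-at-random assumption, so its agreement says little about informative dropout

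*SAP article*

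**What the plan says.** Under Effectiveness outcome analyses, the continuous secondary outcomes are handled so: "between-group comparisons will be conducted using multiple linear mixed-effects regression combining all available post-randomisation measurements". RMDQ and EQ-5D-5L are collected at months 3, 6, 9 and 12.

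Under Handling of missing data, the scope of the rule is set by "For the remaining secondary effectiveness outcomes, the number of missing observations will be reported at each relevant timepoint". The rule itself is "In cases where more than 10% of the outcome data is missing, multiple imputations will be used to conduct sensitivity analyses", followed by "The need to impute will be confirmed at the time of the masked review of the data". No imputation model or auxiliary variables are given for these outcomes, and no delta-adjusted, tipping-point or reference-based analysis is stated. The SAP does not name its missingness assumption; missing at random is inferred from the methods.

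The only figure for expected loss is under Sample size and randomisation: "Sample size calculations allowed for 1% loss to follow-up per month".

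The economic evaluation has its own rule: "missing cost and effect data will be imputed using multivariate imputation by chained equations with predictive mean matching", with a complete-case analysis as the sensitivity check.

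**The concern.** A sensitivity analysis for missing data is useful when it changes the assumption that cannot be checked. A likelihood-based mixed model on all available measurements already gives valid estimates if, given what was observed, loss does not depend on the unseen value. Standard multiple imputation needs the same condition. Fed the same variables, it is close to a second computation of the same estimate.

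Informative loss is plausible in this trial. Participants know their allocation, RMDQ and EQ-5D-5L are self-reported, one arm is asked to keep up a walking programme and the other receives nothing, so reasons for leaving may differ by arm.

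What is at stake is how the disability and quality-of-life results are read. If the two analyses agree, a reader may take that as evidence against dropout bias, when it carries little information on that question. Disability also has a possible further role: Sub-group analyses says the moderation work may move beyond the primary outcome if a key secondary outcome such as disability shows a worthwhile effect.

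**Working it through.** **1. The plan's own figure.** Hazard ratio = ln(0.775)/ln(0.70) = 0.715, which needs 279 events (Schoenfeld, 80% power, two-sided 0.05). With exponential event times, uniform 24-month accrual, 12-month minimum follow-up and 1% monthly loss, the event probabilities are 0.449 (control) and 0.351 (intervention), mean 0.400. Then 279/0.400 ≈ 698, the stated total. The sample size is not in question, and the 1% loss enters it as a constant monthly rate.

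**2. Missingness implied by that allowance.** Cumulative loss = 1 − 0.99^m.

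| Month | Loss |
|---|---|
| 3 | 3.0% |
| 6 | 5.9% |
| 9 | 8.6% |
| 12 | 11.4% |

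The mean over the four visits is 7.2%. If the 10% rule is applied per visit, only month 12 triggers it. If it is applied to an outcome over all visits, nothing does. The SAP does not say which is meant. Intermittent missed questionnaires would add to these figures.

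**3. Do the two methods differ when dropout is informative?** Simulation on assumed inputs, not from the SAP: 350 per arm, four visits, SD 4, within-person correlation 0.6, true difference −1.0, 200 replicates, imputation using only the variables in the mixed model.

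| Dropout | Missing at last visit (control / intervention) | Mixed model | Imputation | Mean absolute gap |
|---|---|---|---|---|
| Missing at random | 16.8% / 14.8% | −0.98 | −0.98 | 0.02 |
| Depends on the unseen value, intervention arm only | 14.7% / 19.3% | −1.27 | −1.27 | 0.02 |

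In the second row both methods are off by 0.27. The gap between them is the same in both rows, so it does not tell the two situations apart. The direction of the bias follows from how the dropout was set up.

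**4. What a shifted imputation does.** If imputed final-visit values are shifted by δ in each arm, with proportions missing π, the difference (intervention minus control) moves by π_I·δ_I − π_C·δ_C. In the informative case with δ_I = +2 (0.5 SD) and δ_C = 0, the move is 0.193 × 2 = 0.39, giving −1.27 + 0.39 ≈ −0.89, as simulated. Under missing at random the same shift gives −0.98 + 0.148 × 2 ≈ −0.68. So the shift neither detects informative loss nor corrects for it; both values miss −1.0. It shows how far the result moves per unit of departure.

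**5. Size at the plan's allowance.** With 11.4% missing in each arm at month 12 (δ in SD units, assumed):

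| δ_I | δ_C | Move in difference (SD) |
|---|---|---|
| 0.5 | 0 | 0.114 × 0.5 = 0.057 |
| 1.0 | 0 | 0.114 × 1.0 = 0.114 |
| 0 | 0.5 | −0.057 |
| 0.5 | 0.5 | 0 |

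A separate simulation (400 trials per δ, 350 per arm, correlation 0.6) agrees. Full-data effects were 0.051 and 0.108 SD, while the mixed model gave −0.005 and −0.006 and imputation −0.006 and −0.006, so both missed 0.056 and 0.114. The two methods' month-12 estimates correlated 0.996.

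**6. Against precision.** About 350 × 0.886 = 310 per arm would be observed at month 12, so the cross-sectional standard error is about √(2/310) = 0.080 SD. The moves of 0.057 and 0.114 SD are about 0.7 and 1.4 standard errors. That is small for a clear result and enough to change a marginal one.

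**The case against.** The best reply is that near-agreement depends on imputing with the mixed model's own variables, and the SAP does not fix the imputation model. The trial collects much that lies outside that model: monthly recurrence reports, quarterly adherence ratings, session attendance, walking diaries and co-interventions. In the economic section the imputation model does include predictors of missingness. Imputation with such variables makes missing at random more credible and can differ from the mixed model. Loss after a reported relapse or reported poor adherence could then be handled; only deterioration never reported before loss would escape. This stands. A reader might infer that imputation is bound to agree with the main result, and the SAP does not support that. What remains is that no such variables are named for RMDQ and EQ-5D-5L, and even rich imputation ordinarily stays within missing at random.

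Three further objections stand:

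- The plan as a whole has another missing-data check, the complete-case analysis in the economic evaluation, so imputation is not the only one. It covers the economic analysis and does not model loss that depends on unseen values.
- Direction is not established. Nothing in the SAP favours loss of worse intervention participants over loss of relapsed controls who receive nothing.
- The illustrated shifts are modest, and the deltas and the correlation are assumptions. The 1% monthly loss is a design allowance, not a forecast.

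It can also be said that an article leaves imputation detail to a fuller document. That is fair for the detail. The point rests on the check the article does name.

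**Conclusion.** The point holds for RMDQ and EQ-5D-5L. The named sensitivity analysis ordinarily shares the main model's missing-at-random assumption, nearly reproduces it when the same variables are used, and therefore gives little reassurance about informative dropout. No departure from missing at random is stated for these outcomes. The 10% trigger does not help: the amount missing does not show whether loss is informative, and the plan's allowance passes 10% only by month 12.

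The size is modest: about 0.06 to 0.11 SD at month 12 for unseen values 0.5 to 1.0 SD different in one arm, with 11.4% missing. This rests on the assumed deltas and on loss equal to the allowance.

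Two stronger readings should not be drawn. One is that the secondary effects are biased in favour of the intervention; the SAP gives no basis for a direction. The other is that the primary result is affected. The imputation rule covers the remaining secondary outcomes, while the primary is handled by censoring ("Participants who are lost to follow-up will be censored on the day they last provided data") and a completeness index, which is a separate question. Physical activity outcomes, analysed by linear regression at each timepoint, also lie outside the point. This is a worthwhile, inexpensive improvement and not an error that undermines the plan.

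**What to change.** In Handling of missing data, for RMDQ and EQ-5D-5L:

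1. State the missingness assumption of the mixed model, and name the imputation variables, including auxiliary data already collected such as monthly recurrence reports and baseline predictors of dropout.
2. After imputing, add a shift δ to the imputed values over a prespecified grid (for example 0 to 1 SD in size), varied separately in each arm and in either direction. Equal shifts in both arms largely cancel, so a common shift is not enough.
3. Report the combinations of shifts at which the conclusion changes, and judge whether they are plausible.
4. Run this regardless of the 10% threshold and without leaving the need for it to the masked review.

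Fix the wording before allocation is unmasked. The cost is a paragraph in the SAP and a few lines of code on top of the imputation already planned. The main analysis and the sample size do not change. The real burden is choosing and defending the grid.
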